#### eHealth Literacy Scale

The eHealth Literacy Scale (eHeals) is an 8-item scale that tends to measure perceived skills at finding, evaluating, and applying electronic health information to health problems [55]. The instrument has been proven to be a reliable and easy-to-use self-report tool and has been used in some studies. The scale is based on a model that distinguishes between 6 types of literacy skills: traditional literacy, health literacy, information literacy, scientific literacy, computer literacy, and media literacy. Accordingly, the eHeals aims to measure a broad overview of literacy skills, which might make it a potential instrument to assess the effects of electronic health literacy–tailored strategies to deliver online information and apps.

#### System Usability Scale

The System Usability Scale provides a “quick and dirty,” reliable tool for measuring a product’s usability [56]. It consists of a 10-item short questionnaire with 5 response options for respondents, ranging from “Strongly agree” to “Strongly disagree.”

#### Think-Aloud Protocol

Think-aloud is a well-established technique for usability assessment, commonly used to determine users’ thoughts and opinions while they perform a list of specified tasks with a system [57]. A think-aloud protocol asks users to express their immediate thoughts and reactions during their interactions with a system. The sessions are normally recorded, or notes are taken [58]. Minimal intervention from the usability tester assures users’ thought processes are not interrupted except to remind them to keep talking. The focus is on understanding users’ decision-making processes and on how users experience the system in their own words. Only a small sample of users is needed due to the extensive, detailed data it provides [59,60].

To guide the usability evaluation, case scenarios were created for what would be considered as normal everyday user interactions with the More Stamina solution. A panel of neurologists, physiotherapists, and designers validated the different scenarios. The specific scenarios patients will have to perform will consist of (1) completing their user profile, (2) creating a new activity for themselves, (3) managing previously recorded activities, (4) planning for a future activity, and (5) responding to one of the integrated surveys (Multimedia Appendix 1).

Participants will be instructed to assess the More Stamina app using the think-aloud method, stating out loud what they are doing, what thoughts come to their minds, and how are they interacting with the app. The facilitator will record comments and actions of the participants with screen-capturing software and an audio recorder.

#### Open-Ended Interviews

Qualitative inquiries are useful to provide insight into complex and multifaceted experiences of individuals when a rich description is the main goal of the study [61]. Participants of our study will be interviewed with open-ended questions to explore their experiences with the mHealth solution. They will be asked to comment on sections of the system they thought were well designed, to comment on sections that were inadequately designed, and to provide any further comments they might have about system usability.

#### User Behavior

Within More Stamina, Stamina Credits are a numeric continuous variable that ranges from 0 to 100 to represent the estimated effort of an activity. This variable is used to gauge how effective the user is in predicting the effort of each individual activity.

User activity patterns over time will be aggregated per week and described. Adherence will be estimated in each follow-up meeting. Adherence with app use will be estimated using the frequency of weekly use throughout the tracking period.

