### More Stamina

More Stamina is a gamified task organization tool designed to help persons with MS manage their energy, to minimize the impact of fatigue on their daily life. The tool acts as a to-do list where users can input the tasks they want to accomplish that day in a simple manner (Figure 1). More Stamina is currently available in English, Spanish, Finnish, and German.

The overall concept is that a person’s energy is represented through a visual metaphor (progress bar) and a symbolic unit that quantifies the amount of estimated effort a given activity might take (Stamina Credits). Users start their day with 100 Stamina Credits and assign them to new activities for that day. As users go through their day and complete the activities, they mark them as done, and the system prompts them to assess whether their effort was underestimated, overestimated, or properly estimated. More Stamina keeps track of these answers as data points and starts analyzing and creating a trend for each activity (eg, “shopping”). Repeated use of More Stamina allows it to learn about the user’s habits, and once sufficient information is gathered on “shopping,” a recommendation feature starts reminding users of their own tendencies.

The app logs user activity through the in-built sensors of the device and is able to monitor the number of steps, walking pace, distances, and GPS positioning. Patient-reported outcomes are available and optional in More Stamina. Standardized tools such as the Fatigue Severity Scale [46] and Chalder Fatigue Scale [47] are loaded into the system. Usage statistics are gathered locally for each added activity to keep track and collect assessments; the user can choose to share these statistics to a secure server for analysis. Users have control as to which information to disclose and with whom, whether it’s personal, clinical, or treatment-related. Additionally, they can opt-in to send de-identified information for research purposes.

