### Objectives

The overall study aims are to explore the feasibility, acceptability, and usability of More Stamina, a mobile app for fatigue self-management for persons with MS.

The specific objectives are to estimate adherence to the use of More Stamina; estimate the effect of More Stamina adherence on behavior change, measured through changes in the amount of activities and amount of estimated energy per activity; estimate the effect of adherence to the use of More Stamina on the perception of fatigue management; validate the value proposition of More Stamina; identify More Stamina user activity patterns of persons with MS; and identify factors associated with the use of More Stamina.

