### Data Analysis

#### Quantitative Analysis

Descriptive statistics will be used to summarize the participants’ background and characteristics. Categorical variables will be presented as absolute and relative frequencies. Continuous variables will be presented as mean and standard deviation or median with interquartile range depending on distribution. A *P* value <5% will be considered statistically significant. Statistical analysis will be performed using STATA v15.

Quantitative analysis will be performed on the data collected through the mHealth solution. A linear regression model will be used to assess the association between the degree of adherence to the app, changes in the amount of activity, and changes in the amount of estimated stamina per activity. The outcome variables will be changes between baseline and final activities, changes in estimated stamina per activity for specific activities selected by the researcher team based on frequency and relevance, and changes in fatigue self-perception. Changes will be calculated considering the baseline measurement and final measurement after the 3-month tracking period. A multivariate linear regression model adjusted for age, sex, and eHEALS will be used. The need for inclusion of other potential confounders will be evaluated.

Participants who are above the median usage of the app will be defined as heavy users. The median is less affected by outliers and skewed data and is usually the preferred measure of central tendency when the distribution is not symmetrical. Potential factors associated with the use of the app will be explored with a univariate logistic regression model.

Qualitative analysis will be performed on the data collected through the think-aloud protocol, individual interviews, and focus groups by using thematic analysis to identify emerging themes [62]. Each transcript will be reviewed and coded independently by 2 researchers. The themes will be combined by agreement of the 2 researchers, involving a third researcher in the event of a disagreement. Major themes and subthemes will be developed via an iterative review process. In order to help ensure the integrity of the content analyses, the guidelines recommended by Shenton [63] will be followed, which include collecting and analyzing data in an iterative process to identify themes and generating an audit trail, among others.

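### Change in Stamina Credits cannot show whether users predict effort better; the ratings that could show it are not used as an outcome

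*Protocol article*

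**What the plan says.** The User Behavior section defines the variable: "Stamina Credits are a numeric continuous variable that ranges from 0 to 100 to represent the estimated effort of an activity". Its next sentence gives the variable a second meaning: "This variable is used to gauge how effective the user is in predicting the effort of each individual activity".

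The More Stamina section of the Introduction explains how credits arise: "Users start their day with 100 Stamina Credits and assign them to new activities for that day". When an activity is marked as done, "the system prompts them to assess whether their effort was underestimated, overestimated, or properly estimated". These answers are stored: "More Stamina keeps track of these answers as data points and starts analyzing and creating a trend for each activity". The app later reminds users of their own tendencies.

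The Objectives section wants the effect of adherence on behavior change, "measured through changes in the amount of activities and amount of estimated energy per activity". The Quantitative Analysis section lists as an outcome "changes in estimated stamina per activity for specific activities selected by the researcher team based on frequency and relevance", taken from baseline to the final measurement. On the model it says: "A linear regression model will be used to assess the association between the degree of adherence to the app", together with those changes. The adjusted model names age, sex and eHEALS and leaves other confounders to be evaluated. The stored under/over/proper rating does not appear among the outcomes or the covariates.

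**The concern.** A prediction does not reveal its own accuracy; that takes a comparison with what happened. The only such comparison in the article is the rating after completion. The article gives the accuracy meaning to the credits, analyses the credits, and leaves the rating out.

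A reader who takes the User Behavior sentence at its word will read the slope of credit change on adherence as evidence about learning. A flat slope would then look like no learning, although it could come from two groups improving in opposite directions. A non-zero slope would have no fixed reading as accuracy: a fall in credits is an improvement for someone who over-estimated and a worsening for someone who under-estimated. The results are meant to inform a larger randomized study, so a misreading could carry forward.

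**Working it through.** The article gives no effect size, standard deviation, power or mix of over- and under-estimators for this outcome, so there is no figure of its own to reproduce beyond the sample size, 3 × 20 = 60. The check is algebra, then simulation under stated assumptions.

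**Algebra.** Let a user's credit value be true effort T plus an error sb, where s = +1 for an over-estimator and −1 for an under-estimator, and b is the size of the error, with mean B. Suppose adherence a (0 to 1) removes a fraction a of the error and T stays fixed.

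- Baseline: T + sb. Final: T + sb(1 − a). Change: −sba.
- With a share p of over-estimators, the mean of s is p − (1 − p) = 2p − 1.
- Slope of mean change on adherence: −(2p − 1)B.

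The slope is zero at p = 0.5 and reaches its full size B when p is 0 or 1. At p = 0.3 it is |2 × 0.3 − 1| = 0.4 of full size. Adding the initial direction s as a covariate does not restore the slope, because the average over the two groups is still what is fitted; a split by direction, or an interaction with adherence, is needed.

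**Simulation.** Assumptions, none from the documents: T = 30 credits, mean error 15 (SD 5), measurement noise SD 5, adherence uniform on 0 to 1, ordinary least squares without covariates. With n = 60, two-sided 5% and 3,000 runs per row:

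| p (share over-estimating) | Slope by formula, (1 − 2p) × 15 | Simulated slope | Credit change significant | Change in absolute error significant |
|---|---|---|---|---|
| 0.5 | 0 | 0.08 | 7.3% | 94.9% |
| 0.4 | 3 | 2.97 | 11.8% | 94.8% |
| 0.3 | 6 | 6.06 | 25.6% | 95.0% |
| 0.2 | 9 | 8.91 | 48.4% | 94.6% |
| 0.1 | 12 | 11.95 | 78.0% | 94.2% |
| 0 | 15 | 15.07 | 98.8% | 94.9% |

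The true learning is the same in every row. The last column uses T, which the study does not measure; it only shows that the improvement is there to be found.

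**A second set of assumptions, with the rating as comparator.** Here the error is about 8 credits, full adherence removes up to 60% of it, and each person rates 20 activities early and 20 late (n = 60, 1,500 runs). For mixes of 50:50, 60:40, 70:30, 80:20 and all one way, credit change was significant in 7.4%, 13.8%, 28.8%, 57.6% and 100% of runs. Change in the proportion rated properly estimated was significant in 98.7%, 98.5%, 98.5%, 98.7% and 97.8%.

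**Other causes of a change in credits.** If effort is not fixed, credits also fall when the activity becomes easier. If the daily 100 credits are spread over k activities, the average is at most 100/k, which falls as k rises. That links this measure to the other behavior-change measure, the number of activities. Neither cause says anything about accuracy.

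**The case against.** The strongest reply is that accuracy was never the target. The objective and the analysis both speak of behavior change, and the outcome matches the objective closely. The accuracy wording is a single sentence that can be read as describing how the app works. The Discussion gives the goal as saving energy, for example by simplifying work, so a fall in credits for an activity can be a meaningful result in its own right. This stands. It is why credit change should keep its place and its regression; making it purely descriptive would leave a stated objective without its analysis.

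It also limits what may be inferred. A reader might conclude that the sign of a non-zero slope reflects nothing but the starting mix of over- and under-estimators. That holds only if true effort is fixed, which the article does not say. A reader might also take roughly 7% against 99% as the expected loss. That contrast needs an even mix and assumed effect sizes; if everyone errs one way there is no loss.

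A further reply is that a condensed article may leave stratification to a fuller plan. That is fair for the split by direction. It does not cover the sentence in User Behavior, which states what the variable measures and is wrong as it stands.

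**Conclusion.** The concern holds in a limited form. Stamina Credits do not gauge how well a user predicts effort, and the planned slope of credit change on adherence, null or not, is not evidence on that question. The cancellation follows from the definition. Its size depends on p, which the documents do not give, and on effort staying constant: with those assumptions it runs from complete at an even mix to none when all users err in one direction. The simulated percentages are illustrations.

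The documents do not support the stronger conclusion that credit change is an invalid outcome to be replaced. This is an exploratory pilot, and the point touches one of two measures under one of six specific objectives. It is a correction worth making, not a reason to hold the study.

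**What to change.** - In User Behavior, replace the sentence on prediction effectiveness: credits record the user's advance estimate, and prediction effectiveness is defined from the ratings given after completion.
- In Quantitative Analysis, add as the prediction-accuracy outcome the change in the proportion of completed, rated activities marked properly estimated. One suitable model is a logistic mixed model per rated activity, with time, adherence and their interaction, and a random effect for participant.
- Keep change in credits per activity as the behavior-change measure in the Objectives. Report it also by initial direction of error (over or under).
- State that the slope of credit change will not be interpreted as evidence on prediction accuracy.

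The cost is analysis work and one more exploratory outcome; the app already prompts for the ratings. The limits should be stated: ratings are the user's own judgment, exist only for completed activities, and reach the researchers only from users who choose to share usage data. How many ratings will be available is not known from the article.

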### Study Flow

Persons with MS from each location will be invited to be part of the study and go through the process of informed consent where they will be briefed about the overall study and their rights as participants (see Ethical Considerations). After providing informed consent, participants will be part of a series of 4 workshops. Prospective monitoring will be carried out for 2 months for all participants at all sites, and daily measurements of More Stamina during that period will be considered.

Encounter 1 will be used to set up user accounts for participants, introduce the More Stamina solution, and install it on their smartphones. Monitoring will begin after the installation of More Stamina. All participants will complete the following standardized tools: EDSS, NeuroQoL, Chalder Fatigue Scale, eHeals, and System Usability Scale.

A subgroup of up to 5 participants per site (total n=15) will be selected for convenience to represent the main themes of this study: time since diagnosis (prolonged or recent), digital health literacy (expert user or beginner user), and disease burden (high or low). This subgroup will go through the think-aloud protocol by performing the specific scenarios and be interviewed about ease, utility, and perceived benefit. The sessions will be digitally audio recorded and video recorded, capturing on-screen navigation on screens.

There will be 3 face-to-face follow up meetings: day 15 (Encounter 2), day 30 (Encounter 3), and at the end of the follow-up at day 60 (Encounter 4). In these meetings, feedback will be obtained on the use of the More Stamina app regarding its functionality, usability problems, daily use, and information concerning disability, quality of life, and adherence. The overall study flow that will be replicated in each site is shown in Figure 3.

**Figure 3 figure3:**
[figure not shown]
Study flow. SUS: System Usability Scale.

### Data Analysis

#### Quantitative Analysis

Descriptive statistics will be used to summarize the participants’ background and characteristics. Categorical variables will be presented as absolute and relative frequencies. Continuous variables will be presented as mean and standard deviation or median with interquartile range depending on distribution. A *P* value <5% will be considered statistically significant. Statistical analysis will be performed using STATA v15.

Quantitative analysis will be performed on the data collected through the mHealth solution. A linear regression model will be used to assess the association between the degree of adherence to the app, changes in the amount of activity, and changes in the amount of estimated stamina per activity. The outcome variables will be changes between baseline and final activities, changes in estimated stamina per activity for specific activities selected by the researcher team based on frequency and relevance, and changes in fatigue self-perception. Changes will be calculated considering the baseline measurement and final measurement after the 3-month tracking period. A multivariate linear regression model adjusted for age, sex, and eHEALS will be used. The need for inclusion of other potential confounders will be evaluated.

Participants who are above the median usage of the app will be defined as heavy users. The median is less affected by outliers and skewed data and is usually the preferred measure of central tendency when the distribution is not symmetrical. Potential factors associated with the use of the app will be explored with a univariate logistic regression model.

Qualitative analysis will be performed on the data collected through the think-aloud protocol, individual interviews, and focus groups by using thematic analysis to identify emerging themes [62]. Each transcript will be reviewed and coded independently by 2 researchers. The themes will be combined by agreement of the 2 researchers, involving a third researcher in the event of a disagreement. Major themes and subthemes will be developed via an iterative review process. In order to help ensure the integrity of the content analyses, the guidelines recommended by Shenton [63] will be followed, which include collecting and analyzing data in an iterative process to identify themes and generating an audit trail, among others.

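### Regressing change in app-logged activity counts on app use can give misleading P values under constant-variance standard errors if use is right-skewed; naming HC3 standard errors is a cheap safeguard

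*Protocol article*

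**What the plan says.** The Quantitative Analysis section of the protocol article names a linear model: "A linear regression model will be used to assess the association between the degree of adherence to the app" and changes in activity and in estimated stamina. Of the outcomes it says "The outcome variables will be changes between baseline and final activities", followed by change in estimated stamina for selected activities and change in fatigue self-perception. It adds an adjusted version: "A multivariate linear regression model adjusted for age, sex, and eHEALS will be used". The decision rule is that a P "value <5% will be considered statistically significant".

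Three other statements fix what the first outcome and the regressor are:

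- The Objectives describe behaviour change as "measured through changes in the amount of activities and amount of estimated energy per activity", so the first outcome is a change in a number of activities.
- Quantitative Analysis gives the source: "Quantitative analysis will be performed on the data collected through the mHealth solution".
- The User Behavior section defines the regressor: "Adherence with app use will be estimated using the frequency of weekly use throughout the tracking period". It does not say whether frequency means days per week or number of sessions.

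Skewness is mentioned once, to justify splitting users at the median: "The median is less affected by outliers and skewed data". The article does not take this up for the linear model. It names neither a standard-error estimator nor the expected distribution of use.

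**The concern.** An activity enters the data only when the user logs it. A person who opens the app often will plausibly log more, and the difference between two large counts varies more than the difference between two small ones. The residual variance then rises with adherence, which is the regressor.

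Default linear-regression standard errors assume one common residual variance. If a few heavy users combine high leverage with high variance, those standard errors are too small, and a slope of zero is declared significant more often than 5% of the time. If most people use the app heavily and a few do not, the error goes the other way and the test is conservative.

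Estimating the effect of adherence on behaviour change is a specific objective, and the Discussion presents the pilot as groundwork for a larger randomised study. A falsely precise adherence association would be an unsafe input to that design.

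**Working it through.** **Inputs from the article.** n=60 (3 sites × 20); threshold 5% (sidedness not stated, two-sided assumed); adjustment for age, sex and eHEALS; outcome a difference of app-logged counts; regressor the weekly frequency of use. The article gives no standard deviation, effect size or power figure, so there is no stated figure to reproduce.

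**Assumed, because the article does not give them.** The distribution of use x, the mean logged count per unit of use, the overdispersion, and whether the baseline count scales with later use.

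**Why the variance rises.** Take two independent Poisson counts, each with mean m·x. Their difference has variance 2m·x, which is proportional to use. With negative binomial counts of dispersion d it is 2(m·x + d·m²·x²), which rises faster.

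**Formula for variance c·x.** Let Sxx = Σ(x − x̄)².

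- True slope variance: c[Σ(x − x̄)³ + x̄·Sxx]/Sxx²
- Nominal slope variance: c·x̄/Sxx
- Ratio: 1 + Σ(x − x̄)³/(x̄·Sxx) = 1 + skewness × CV of use

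The sign of the skewness therefore decides the direction of the error, and symmetric use leaves the level intact.

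**Example.** Use on 0-7 days shaped as Beta(1,3) has CV 0.775 and skewness 0.861. The ratio is 1 + 0.775 × 0.861 = 1.67, and its square root is 1.29. The implied type I error is 2 × [1 − Φ(1.96/1.29)] = 0.13. Simulation with Poisson counts gives 12%.

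**Simulated type I error at n=60.** The model has use plus three covariates, the true slope is zero, and the standard errors assume constant variance.

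| Assumed use | Baseline and final counts both scale with use | Baseline count does not scale |
|---|---|---|
| Right-skewed | about 12-24% | about 6-13% |
| Uniform or U-shaped | about 5-7% | within the same range |
| Left-skewed | about 2-4% | within the same range |

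In the right-skewed row, use bounded at 7 days (Beta(1,3) or Beta(0.7,1.8), mean count 2 × use-days) gives 12-20% when both counts scale. With a common baseline mean of 10 and the mean trend removed it gives 6.6-9.3%. The drop is expected. With a fixed baseline the Poisson variance is 10 + 2x, running from 10 to 24 over 0-7 days; when both counts scale it is 4x, running from 0 to 28.

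**Check and sensitivity.** A separate simulation (mean count 3 × use, 6,000 runs per case) with constant error variance rejected 4.5-5.2%, so it recovers the nominal level. With unbounded use it gave 14-26% for gamma, 16-30% for lognormal (σ=0.6), 21-37% for exponential and 33-53% for lognormal (σ=1). These need a use measure with no ceiling and strong skew. At n=48 the results were nearly the same.

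**Robust standard errors at n=60, same simulation.**

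- HC3: 3.5-4.9% for bounded symmetric or left-skewed use; 6.4-8.9% for gamma, exponential or lognormal (σ=0.6); 9.2-11.3% for lognormal (σ=1).
- HC1, which Stata's `vce(robust)` gives: 10.6-26.7% across the right-skewed cases.

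**The case against.** The strongest objection is that the article never says ordinary or constant-variance standard errors. It says linear regression in Stata, and a linear regression with HC3 errors satisfies that wording. A journal article commonly leaves the variance estimator to the full protocol or analysis plan, and neither is shown. This stands: the missing estimator is not in itself an error. What remains is that the article chooses a linear model and a significance threshold for a count difference whose variance is tied to the regressor by construction, and the default for that choice is constant variance.

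Second, a reader might infer that the article predicts right-skewed use and that its P values will therefore be wrong. The text does not support this. The remark on skewness is a general argument for the median and gives neither direction nor size. If use means days per week and is roughly symmetric, the level is nearly kept; if most people use the app on most days, the test is conservative.

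Third, the larger figures assume that baseline logging scales with later use. Monitoring begins at installation, so the baseline period follows a facilitated set-up and need not reflect later adherence. This also stands, which is why both columns are shown.

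Fourth, the mechanism is argued for one of three outcome types. Stamina per activity is bounded at 0-100, and fatigue self-perception is not a count of logged activities. Nothing here shows a problem for either.

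Finally, this is a pilot of feasibility, acceptability and usability that disclaims assessing health outcomes. That limits the consequence, but it does not make a misleading P value useful.

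**Conclusion.** The point holds as a conditional one. For the change in activity counts, constant-variance standard errors can be materially too small if app use is right-skewed and logging scales with use: about 12-24% type I error against a nominal 5%, or about 6-13% if only the final count scales. With uniform or U-shaped use the departure is small (about 5-7%), and with left-skewed use the test is conservative (about 2-4%). The upper ends depend on the assumed shape and dispersion and should be read as orders of magnitude.

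The slope is not biased by this; only its standard error, interval and P value are affected. The documents do not support the stronger readings that the planned P values are wrong whatever the pattern of use, or that all three outcomes are affected. This is an inexpensive improvement to the plan, not a fatal flaw.

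**What to change.** In Quantitative Analysis, state that the regression of change in activities on adherence, unadjusted and adjusted, uses HC3 heteroscedasticity-robust standard errors, and that the slope is reported with a 95% confidence interval based on them. Name HC3 explicitly, because Stata's `vce(robust)` stays anti-conservative at this sample size. HC3 may also be used for the other two outcomes for consistency, although no need for it is shown there.

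A negative binomial model of the final count with log baseline as covariate is not recommended as a substitute. It replaces the planned change with a different estimand and is undefined when the baseline count is zero.

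Cost: one software option and no new data. Under right skew the intervals become about 10-55% wider, which reflects the uncertainty that the default understates. Under heavy skew about 6-11% type I error remains, so borderline P values should still be read with caution.
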